**Figure 1 F1:**
[figure not shown]
Flow chart of the study design.

The study was performed at three cities in Finland (Helsinki, Jyväskylä, and Kuopio) by the local universities (University of Helsinki, University of Jyväskylä, and University of Eastern Finland, Kuopio). In addition, VTT Technical Research Center of Finland (Tampere, Finland), Finnish Institute of Occupational Health (Helsinki and Oulu), and companies Duodecim Medical Publications Ltd. (Helsinki, Finland), Firstbeat Technologies Ltd. (Jyväskylä, Finland), Vivago Ltd. (Espoo, Finland), Finnish Red Cross Blood Service (Helsinki, Finland), and Valio Ltd. (Helsinki, Finland) participated in performing the study. The study was approved by the ethics committee of the Central Finland Health Care District, and registered with ClinicalTrials.gov with the identifier NCT01738256.

The study was carried out in two phases. The first phase started in September 2012 and the second phase in January 2013. The study included pre-measurements before the 8-week interventions, post-measurements 10 weeks after the pre-measurements, and follow-up measurements six months after the post measurements (36 weeks from pre-measurement). The last measurements were collected in December 2013.

### Study population

The recruited participants (n = 339, Figure 1) were either overweight or obese and reported psychological stress symptoms. The inclusion criteria were: 1) Body Mass Index (BMI) 27–34.9 kg/m^2^, 2) perceived psychological stress (at least 3/12 points in General Health Questionnaire [32], and 3) the possibility to use computer with internet connection. The exclusion criteria were: diagnosed severe chronic illness (symptomatic cardiovascular disease, Type I or II diabetes, severe psychiatric conditions or substance abuse), medical surgery within the past 6 months, heart attack/stroke within past 6 months, kidney disease requiring dialysis or other disabilities/illnesses affecting substantially physiological or mental health, regular use of cortisone pills, pacemaker, eating disorder (bulimia), disability pension for psychological reasons, pregnancy or breastfeeding within the past 6 months, shift work (in three shifts) or night work, psychotherapy or other psychological or mental treatment at least twice a month, and participation in other intervention studies during the present study.

### Procedure for recruitment, randomization and allocation

The participants were recruited by using advertisements in local newspapers. All the participants took part in the study on volunteer basis. The initial exclusion criteria were assessed through phone calls and by using electronic questionnaire for reported distress. The participants who passed the initial screening were randomly allocated into one of the three intervention groups (Internet, Mobile, Face-to-Face), or into a control group. After randomization, participants with predetermined abnormalities in baseline laboratory examinations were excluded from the study (see Figure 1). At the baseline visit to the study center the blood samples were drawn for determining health status and excluding volunteers with unknown/undiagnosed chronic disease or other health problem. The measurements for liver, thyroid glands and kidney function as well as glucose and lipid metabolism were taken. If there was a value outside reference values, the participant was excluded before starting the actual interventions. Written informed consent was obtained during the laboratory examination. Randomization was done by a university statistician using a table of random numbers (in batches of four). An independent person outside of the research group prepared envelopes containing the randomization number, study ID and group number by center. The envelopes were opened in the order participants passed the initial screening following ‘concealment of allocation’ principle.

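### The allocation envelope is opened on passing initial screening, before written consent and the laboratory exclusions, so who starts the trial can depend on the arm drawn

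*Protocol article*

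**What the plan says.** All of the relevant text is in the protocol article, Methods/Design, under Procedure for recruitment, randomization and allocation.

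- Screening: "The initial exclusion criteria were assessed through phone calls and by using electronic questionnaire for reported distress".
- Allocation: "The participants who passed the initial screening were randomly allocated into one of the three intervention groups", or to control. On timing and concealment: "The envelopes were opened in the order participants passed the initial screening following ‘concealment of allocation’ principle". An independent person prepared the envelopes, by center.
- Baseline visit: "At the baseline visit to the study center the blood samples were drawn for determining health status and excluding volunteers" who have a previously unrecognised health problem.
- Consent: "Written informed consent was obtained during the laboratory examination".
- Exclusion: "After randomization, participants with predetermined abnormalities in baseline laboratory examinations were excluded from the study". The same paragraph then puts the rule differently: "If there was a value outside reference values, the participant was excluded before starting the actual interventions".

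The Control group section says that controls were measured but received no active intervention. Under Aim and main hypotheses, H1 compares each intervention separately with that control.

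**The concern.** Sealed envelopes protect an allocation only until they are opened. Here the steps that decide who actually enters the trial (attending the visit, signing consent, passing the laboratory check) come after opening. The arms differ greatly in appeal: a series of group sessions, a smartphone with a training application, an Internet coaching program, or nothing. Volunteers who answered a newspaper advertisement hoping for help have an obvious reason to drop out before consent if they draw the last of these.

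If people leave at this stage for reasons linked to both arm and prognosis, the groups that start are no longer the groups that were randomised. H1 is the most exposed hypothesis, because each of its contrasts has the no-treatment arm on one side. The missing-data method in the Statistical analysis section, FIML under a missing-at-random assumption, cannot repair the loss of people who were allocated but never measured, since they contribute no outcome data.

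**Working it through.** **1. Order of events.** That the laboratory exclusion follows randomisation is stated outright. That consent also follows allocation comes from two sentences read together: allocation is tied to passing the initial screening, and consent is tied to the laboratory examination, which is not part of that screening. The sequence is therefore:

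1. phone calls and electronic questionnaire passed
2. envelope opened
3. baseline visit with blood draw and written consent
4. laboratory exclusion
5. intervention starts

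**2. What each step after opening can do.**

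- *Attendance and consent (step 3).* These are the participant's decisions. Nothing in the section says that the arm was withheld until they were made. This is the main route by which loss could depend on arm.
- *Laboratory exclusion (step 4).* The values precede any treatment. A fixed rule applied without knowledge of the arm removes people at the same expected rate from every arm and does not bias the comparison. It becomes a concern for two reasons. No blinding of the decision is stated. The rule also appears once as a list of abnormalities set in advance and once as any value outside the reference range, and these need not exclude the same people.

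**3. Size: illustration only.** None of the plan's figures bears on this point; its power statement neither supports nor weakens it. Figure 1 could not be seen, so pre-start losses by arm are unknown. It is also unclear whether 339 is counted before or after the laboratory exclusions: the Abstract has 339 both recruited and randomised, while Study population calls them recruited.

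Assumptions: a net fraction *f* of one arm is lost selectively, and those lost differ from those kept by *g* SD. The mean of the whole arm is (1 − f) × kept + f × lost, so the kept mean is displaced from it by

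bias = f × g (in SD).

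With 80 per arm (the lower end of the plan's 80–85) and no true effect, SE = √(2/80) = 0.158 SD. The two-sided rejection rate at 0.05 is

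1 − Φ(1.96 − bias/SE) + Φ(−1.96 − bias/SE).

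| f | g | bias (SD) | rejection rate |
|---|---|---|---|
| 0 | any | 0 | 0.050 |
| 0.05 | 0.5 | 0.025 | 0.053 |
| 0.10 | 0.5 | 0.05 | 0.062 |
| 0.15 | 0.5 | 0.075 | 0.076 |
| 0.10 | 1.0 | 0.10 | 0.097 |
| 0.15 | 1.0 | 0.15 | 0.158 |

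For scale, the plan calls a between-group effect of 0.2 small. The values of *f* and *g* are not taken from the article, and the table is for an unadjusted contrast of means.

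**The case against.** The strongest reply is that nothing shows anyone left because of their arm. The article reports no refusals after allocation, does not say when participants learned their arm, and refers to Figure 1 for the exclusions, so the counts by arm may already be published there. The Statistical analysis section also promises control for baseline differences. A stable difference in level among those who start would appear at baseline and be largely removed, leaving mainly the bias that arises if leavers would have changed differently over time. The table above does not model that. All of this stands: it limits what can be said about occurrence and size. It does not alter the order of events, and it does not supply a statement that the arm was withheld until consent and laboratory decisions were complete.

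A reader might go further in four ways that the text does not support:

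- *The laboratory exclusions in themselves bias the comparison.* They rest on pre-treatment values, and a fixed rule applied blind to arm would be harmless. The mention of unrecognised disease gives the purpose of the blood draw; it is not a discretionary criterion.
- *All baseline measures were taken with the arm known.* The order is clear only for the laboratory sample and consent. The timing of questionnaires and device recordings relative to the envelope is not given.
- *Batches of four let staff predict the fourth allocation.* That assumes each batch holds every arm once and that the same staff saw the earlier envelopes; the article states neither. It would also act before opening, so it is a different problem from loss afterwards.
- *Everyone randomised can be kept in the analysis through FIML.* People who never attended or consented have no outcome data to model, and such data as exist may not be usable.

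**Conclusion.** The point holds in a limited form. Allocation is disclosed before consent and before final eligibility is settled, so the concealment that the article claims does not cover the steps that decide who starts. Arm-dependent refusal, especially in the no-treatment control, is the main risk. The laboratory exclusion adds a lesser one through unstated blinding and a rule worded in two ways.

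The order of events is well supported. The occurrence and size of bias are not established. If pre-start losses do not depend on arm, the bias is zero; under the assumed losses above it runs from 0.025 to 0.15 SD before baseline adjustment. This should be fixed through re-checking, disclosure and cautious interpretation. It does not show that the trial's comparisons are invalid.

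**What to change.** **For any further phase.** Change the allocation paragraph so that the envelope is opened only after written consent is signed and the laboratory results are complete. The cost is a later opening of the envelope.

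**For the existing data.** Measurement ended in December 2013, so the sequence itself cannot be changed. Instead:

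1. Reconcile the two wordings of the laboratory rule from the trial's records, and state the one that was set in advance.
2. Have someone unaware of arm re-apply that rule to all consented participants with a baseline sample. Analyse in the allocated arm everyone who does not meet it and has usable data.
3. Report by arm the numbers randomised, not attending or not consenting, excluded on laboratory values, and started. Say at which of these stages 339 is counted. If Figure 1 already gives these counts, refer to it and fill only the gaps.
4. If pre-start losses differ by arm, qualify the claim of concealed allocation and limit the H1 conclusions accordingly. People who never consented can be counted but not modelled.

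The cost is a re-check of laboratory records and, where needed, a fuller flow table.

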### Interventions

#### Internet-based coaching

The Internet-based intervention (Table 1) consisted of a 12-week program without any face-to-face contact (Duodecim Virtual Health Check and Coaching program). The intervention combined the assessment of psychological resources and health related behavior to provide users with a comprehensive view of their health and life situation and ways to improve it. With the support of the assessment, the users could choose between coaching programs to improve positive life skills and to change health related behaviors.

**Table 1 T1:** Content of the Internet intervention

**Content**	**Key points**
Health questionnaire	Estimate of life expectancy, coronary heart disease, stroke and diabetes risk. Description of one’s life habits and behaviors impacting on health and ways to influence them
**Coaching programs**	
Each program includes a weekly message.	
In weight management, healthy diet, exercise, sleep improvement and alcohol use management programs the user has an option to record follow-up information about relevant behavior or parameter:	
a) Weight management	Messages consist of information, practical advice and exercises on weight management (e.g. managing appetite, eating, portion size, buying food), and link to further readings.
b) Healthy diet	Messages about healthy diet and practical advice for improvement, and also links to further readings.
c) Exercise	Messages include information about health related physical activity and link to further readings. Message contains also advice or practice.
d) Stress and life management	Optional: Stress management, Good deeds, Optimism, Human relations, Social relations, Positive interaction in relationships, Resolving conflicts in relationships, Coaching exercises for families with children. The weekly coaching message includes information, practical advice, and exercise about stress or life management and link to further readings.
Optional:	
e) Sleep improvement	Information, practical advice and exercises on good sleep (e.g. sleep hygiene, environment, relaxation) and link to further readings. Message contains also advice or practice.
f) Alcohol use management	Cognitive behavioral program to analyze reasons and situations of alcohol use and advice to avoid excess use.
g) Smoking cessation	Cognitive behavioral program to analyze reasons and situations of smoking, mental exercise, and support for quitting.

In the Health Check, the users filled out a health questionnaire assessing key health determinants, lifestyle factors, emotional well-being, and performance (Figure 2). On the basis of the assessment, the users received estimations, including a prognosis of average life expectancy, coronary heart disease, stroke and diabetes risk, as well as a description of their habits and behaviors impacting their health (Figure 3). The questionnaire and algorithms assessing health risks were based on the Finnish health check and follow-up study Finriski, having up to 30 years follow-up data on a population sample more than 10 000 people [33].

**Figure 2 F2:**
[figure not shown]
Screenshots of the internet application.

**Figure 3 F3:**
[figure not shown]
Screenshots of the internet application.

On the basis of the health check feedback, users could choose optional coaching programs for weight management, healthy diet, exercise, sleep improvement, alcohol consumption management, smoking cessation, and mental well-being (stress management, gratitude, forgiveness, good actions, optimism, positive interaction in relationships and resolving conflicts in relationship). Participants were nonetheless commended to choose primarily from the following three programs: Stress and life management, Nutrition, and Exercise. The programs were designed to support improvements in the health and well-being habits and behaviors.

In the coaching program, users received a weekly coaching message including information about the chosen topic and a link to further information. In addition, the message contained advice or exercise, through which an individual could improve awareness of his/her behavior and practice skills to develop habits that support wellbeing. The weekly message also included feedback based on entries made by the respective user. The users had an option to record follow-up information about their lifestyles (weight, physical activity, nutrition, alcohol consumption and smoking). During the program, users could monitor their progress through graphs, make new health checks, and choose new coaching programs (Figure 4).

**Figure 4 F4:**
[figure not shown]
Screenshots of the internet application.

Coaching programs for weight management, sleep improvement, exercise, alcohol consumption management, and smoking cessation were based on cognitive-behavioral practices on lifestyle changes [34-37]. The test and coaching programs for mental well-being have been developed along the outlines described by several authors [38-40] showing that the cognitive behavioral coaching program to develop optimism, gratitude and other life skills are effective in traditional writing exercise and web-based coaching programs [38,41]. The validity of the variables has been tested in a large cross-sectional study where more than 130 000 Finns completed the questionnaire [42].

### Mobile-based intervention

The participants in the Mobile-based intervention were invited in a group meeting that consisted of a brief overview of Acceptance and Commitment Therapy (ACT) principles. In the meeting, the participants were given Android smartphones that were pre-installed with a stand-alone mental wellness training application called Oiva. They were instructed to use Oiva for the upcoming 8 weeks at their own. The application contained short exercises that taught ACT skills to be applied in daily life. The mobile application delivered an ACT-based intervention program similar to the Face-to-Face group. Prior to the present trial, the application had been piloted in a feasibility study with a sample of office workers with stress symptoms [29].

The content of the application was divided into four intervention paths: Mindful Mind, Wise Mind, Values, and Healthy Body (Table 2). The first three paths demonstrate core processes of ACT and the fourth path applies ACT-based approach on physical well-being. The application contained altogether 46 exercises in text and audio formats, as well as introduction videos for each path and section. The program did not include psycho-education on healthy diet or physical activity, only a hyperlink to a public nutritional website was provided.

**Table 2 T2:** Content of the four paths in the mobile intervention

**Topic of the path**	**Content**	**Key points**
Mindful mind	Five mindfulness exercises	Contact with the present moment.
		Focusing fully on one’s inner or outer experiences.
		Acting mindfully.
Wise mind	Observation: six exercises	Observing thoughts without being caught up in them.
	Acceptance: four exercises	Making room for unpleasant feelings, sensations, urges, and other private experiences; allowing them to come and go without struggling with them.
Values	Values: seven exercises	How I use my time in my current life?
		How mindfulness-skills can improve wellbeing?
		What are the most important values for me?
		Am I living according to my values?
	Value based actions: seven exercises	What are my specific goals and actions that support my valued behavior?
Healthy body	Relaxation: six exercises	Relaxing and listening to my body.
	Mindful eating: six exercises	Exercising mindful eating. What is my typical meal rhythm?
	Physical activity: five exercises	Everyday physical activity in small steps.
	Eleven gymnastic video clips	

Figure 5 presents examples of the user interface of the application. The main screen (Figure 5a) contained a flower-shaped menu through which different paths could be accessed. The main screen also provided access to a diary (Figure 5b), list of favorite exercises, and introduction to the application in text and video formats (Figure 5c). Each petal represents one of the paths, which were numbered according to their recommended order. Each path consisted of 1–4 subsections (“steps”), which included 5–8 exercises (Figure 5d). There was an introduction in text and video formats to each path and step, informing users about the processes and skills.

**Figure 5 F5:**
[figure not shown]
**Screenshots of the mobile application. (a)** main screen, **(b)** diary, **(c)** introduction video, **(d)** top menu of Mindful Mind, **(e)** exercise introduction screen, **(f)** audio exercise, **(g)** text exercise, **(h)** exercise reflection screen.

Most of the exercises were short and took about 1–3 minutes to be completed (Figure 5e-h). This aimed at making exercises easy to perform in any situation. Each exercise began with an introduction presenting the purpose, duration and instructions of the exercise (Figure 5e). The users could choose to exercise by listening (Figure 5f) or by reading (Figure 5g). After each exercise, a reflection screen (Figure 5h) summarized the skills learned from the exercise and enabled users to write notes and reflections in their diary (Figure 5b). The notes were saved in the diary and could be accessed later. The application smoothly guided users through the intervention program without restricting free navigation. Paths, steps, and exercises were numbered in the recommended order and the next suggested item was dynamically highlighted (Figure 5a and d). However, all paths and exercises were accessible from the very beginning.

### Face-to-face group intervention (Face-to-Face)

The ACT-based face-to-face group intervention consisted of six group sessions during 8-week period of time, with each session lasting for about 90 minutes (see Table 3). Each group consisted of 6–12 participants and was instructed by a psychologist. Three psychologists acted as coaches. All of them were trained in ACT approach, had experience in ACT interventions, and had a manual of the program to follow. The participants were given a workbook that contained short descriptions of the sessions, exercises, and individual reflections and notes.

**Table 3 T3:** Content of the six group sessions in the Face-to-Face group intervention

**Topic of the group session**	**Content**	**Key point of the session**
My life here and now	Values: one exercise	How I use my time in my current life?
	Mindfulness: one exercise	Contact with the present moment.
Values and mindful living	Values: three exercises	How mindfulness-skills can improve wellbeing?
	Mindfulness: one exercise	What are the most important values for me?
	Mindful eating: one exercise	Am I living according to my values?
Value-based actions and barriers	Action: one exercise	What are my specific goals and actions that support my valued behavior?
	Mindfulness: one exercise	My subjective barriers or reasons connected to healthy eating or physical activity.
	Observation: three exercises	
The observing self and acceptance	Observation: one exercise	Observing thoughts without being caught up in them (defusion).
	Acceptance: three exercises	Making room for unpleasant feelings, sensations, urges, and other private experiences; allowing them to come and go without struggling with them.
	Relaxation: one exercise	Can you accept yourself as you are?
Mindful eating	Mindfulness: one exercise	Exercising mindful eating.
	Mindful eating: three exercises	What is my typical meal rhythm?
Summary and reflection	Observation: one exercise	What have I learned?
	Values: one exercise	How to continue with lifestyle changes?
	Acceptance: one exercise	

The intervention program aimed to support lifestyle changes and to enhance well-being through committed and concrete actions based on the personally important values – the most important directions in life. The program started with an analysis of own life situation and reflections about values and important things in life. After the value clarification, the participants made concrete action plans and defined their own goals. The emphasis was placed on small and feasible actions that lead to better life according to personally chosen values. In order to achieve the set goals, the participants were taught acceptance and mindfulness skills and new ways to deal with the barriers of action. The purpose of teaching acceptance and mindfulness skills was to increase the ability to become aware of one’s own thoughts, emotions and instinctive behavior patterns. By noticing these instinctive thinking styles or routines, and by producing greater psychological flexibility, the participants were expected to have better skills to consciously change their behaviors in everyday life.

Every session included mindfulness exercises, pair and group discussions, and homework related to the topic of the session. The intent behind homework was to encourage participants to work with the topics between the sessions and apply learnt skills into their own living context. The group leader’s role was to introduce the topics, teach new skills, lead the on-going discussions and provide a context in which participants are willing to share their own experiences, thoughts, and feelings. The program did not include psycho-education on healthy diet or physical activity, only a hyperlink to a public nutritional website was provided.

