### Aim and main hypotheses

The overall aim of the present study was to investigate the effect of three novel low intensity psychological interventions for metabolic syndrome risk factors, psychological flexibility and general well-being among obese individuals experiencing stress. The purpose was to study (a) the effects of minimal contact web-based CBT intervention including an approach of health assessment and coaching methods (Internet), (b) the effects of mobile-based intervention containing mindfulness, acceptance and value-based exercises (Mobile), and (c) the effects of face-to-face group intervention using mindfulness, acceptance and value-based approaches (Face-to-Face) in a controlled study design, where control (Control) received no treatment, but the same measurements were completed for all the groups. Thus, both technology-based low intensity self-help interventions offered minimal contact, and they were compared to a brief group intervention. Moreover, we were interested in studying acceptability, applicability, perceived benefits, user experiences, and usage of the said interventions.

The three interventions groups, and the control group were compared based on changes in lifestyle measures (e.g. food and nutrition intake, meal patterns, physical activity, sleeping habits), psychological measures (e.g. psychological flexibility, perceived stress, depression symptoms, quality of life, perceived quality and quantity of sleep), clinical and biochemical variables (e.g. BMI, body composition, circulating glucose, insulin, lipids, stress and inflammation indicators), other physiological measurements (e.g. objective sleep measurements, heart rate variability-based recovery from stress), and user experiences (e.g. experiences with the interventions, actual usage, realization of exercises presented in interventions). We formulized the following hypotheses:

H1: Participants who receive any of the three interventions would show improvements in lifestyle and psychological measures, and clinical, biochemical, and physiological variables as compared to the control group. Each intervention group is compared with the control condition separately.

H2: Participants who receive any of the three interventions will show equal positive changes in lifestyle, and psychological measures, and clinical, biochemical, and physiological variables when the interventions are compared with each other.

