### Statistical analysis

Data will be analyzed using the IBM SPSS statistics version 19.0 or newer and Mplus statistical package 7.1 [70]. Analyses will be controlled for possible baseline differences between the groups. Differences in the stability of the outcome measures between the groups will be examined using multiple-group modeling techniques. Full information maximum likelihood (FIML) estimation under the assumption of data missing at random (MAR) will be used in analyzing incomplete data. As the normality assumption is violated, maximum likelihood with robust standard errors (MLR) will be used. The significance level of the study will be set at 0.05. Cohen’s *d* will be used to estimate the effect size, and to reflect the clinical significance of the interventions. A between group effect size of 0.2 is considered small, 0.5 medium, and 0.8 large [71]. A within group effect size of 0.5 is considered small, 0.8 medium, and 1.1 large.

Power calculations were performed in order to determine the sufficient sample size to detect the significant intervention effect at a significance level of α = 0.05. Analysis was conducted for one of the primary outcome measures, depression symptoms (BDI-II). On the bases of our earlier studies using similar brief intervention procedures [72] we expect that the Post-measurement difference between the intervention and control group to be approximately 10 scores. A sample size of 320 (80–85 per group) was expected be sufficient at the power level of 1.00.

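### The described analysis and sample size make no allowance for clustering by therapy group in the Face-to-Face arm

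*Protocol article*

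**What the plan says.** The Protocol article allocates individuals to four arms by numbered envelopes (Procedure for recruitment, randomization and allocation). Face-to-Face participants then attend six sessions of about 90 minutes over eight weeks. On group size and leadership it states: "Each group consisted of 6–12 participants and was instructed by a psychologist. Three psychologists acted as coaches". Interaction is part of the treatment: "Every session included mindfulness exercises, pair and group discussions, and homework related to the topic of the session" (Face-to-face group intervention).

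The other arms have no sustained groups. Internet involves no face-to-face contact, Mobile has one introductory group meeting followed by use of the application alone, and control receives no intervention.

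For H1, "Each intervention group is compared with the control condition separately"; for H2, the interventions are compared with one another (Aim and main hypotheses).

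The Statistical analysis section says: "Differences in the stability of the outcome measures between the groups will be examined using multiple-group modeling techniques". Incomplete data are handled by full-information maximum likelihood. The robust estimator is given one reason: "As the normality assumption is violated, maximum likelihood with robust standard errors (MLR) will be used". The sample size is 320, or 80–85 in each arm, with a stated power of 1.00 for a difference of about 10 BDI-II points. The section names no therapy-group or psychologist term, no cluster-level variance, no ICC and no design effect.

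**The concern.** The design is partially nested: one arm is clustered after randomization and three are not. People who share six sessions, discussions and a leader may end up with correlated outcomes. If so, the Face-to-Face mean carries less information than the same number of independent people would give.

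The consequence differs by hypothesis.

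- **H1.** Face-to-Face against control would be declared significant too often.
- **H2.** This hypothesis predicts equal change. Standard errors that are too small produce spurious differences between Face-to-Face and the technology arms. Where no difference is found, the interval around it is too narrow, so equality looks more precisely established than it is.

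Internet and Mobile against control are essentially unaffected, so the three interventions would not be judged against control on the same footing.

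**Working it through.** **Inputs from the Protocol article.** Group size m = 6 to 12; three psychologists; 80–85 per arm; significance level 0.05; BDI-II difference of 10 points.

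**Assumptions.** ICC 0.01 to 0.10 (not given); two-sided test (not stated); equal arm sizes and equal total variances; BDI-II SD 10, 15 or 20 (not given); no clustering in the comparator, which for Mobile ignores the single introductory meeting.

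**Number of therapy groups.** 80/12 = 6.7 and 85/6 = 14.2, so about 7 to 14.

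**The stated power first.** Power = Φ(10/(SD·√(2/n)) − 1.96). With n = 80:

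- SD 10: Φ(6.32 − 1.96) = 0.99999
- SD 15: Φ(4.22 − 1.96) = 0.988
- SD 20: Φ(3.16 − 1.96) = 0.885

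The stated 1.00 is plausible for a moderate SD. It cannot be verified because no SD is given.

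**Effect of ignoring the groups.**

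- Design effect in the Face-to-Face arm: DE = 1 + (m − 1)·ICC
- Effective n in that arm: 80/DE
- True over naive standard error of a contrast with an unclustered arm: r = √((DE + 1)/2)
- Type I error at nominal 5%: 2·(1 − Φ(1.96/r))

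Worked case, m = 9 and ICC 0.05: DE = 1 + 8 × 0.05 = 1.40; effective n = 80/1.40 = 57; r = √(2.40/2) = 1.095; 1.96/1.095 = 1.79; type I error = 7.4%.

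| ICC | m | DE | Effective n (of 80) | r | Type I error |
|---|---|---|---|---|---|
| 0.01 | 6 | 1.05 | 76 | 1.012 | 5.3% |
| 0.01 | 12 | 1.11 | 72 | 1.027 | 5.6% |
| 0.02 | 6 | 1.10 | 73 | 1.025 | 5.6% |
| 0.02 | 12 | 1.22 | 66 | 1.054 | 6.3% |
| 0.05 | 6 | 1.25 | 64 | 1.061 | 6.5% |
| 0.05 | 9 | 1.40 | 57 | 1.095 | 7.4% |
| 0.05 | 12 | 1.55 | 52 | 1.129 | 8.3% |
| 0.10 | 6 | 1.50 | 53 | 1.118 | 8.0% |
| 0.10 | 9 | 1.80 | 44 | 1.183 | 9.8% |
| 0.10 | 12 | 2.10 | 38 | 1.245 | 11.5% |

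The ratio r and the type I error do not depend on n, so they are the same at 85 per arm. They also apply to Face-to-Face against Internet or Mobile. In the worked case a nominal 95% interval for an H2 contrast covers about 100 − 7.4 = 92.6%.

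**Power with clustering.** Replace √(2/n) by √((DE + 1)/n), with n = 80. The range runs from the mildest case (m = 6, ICC 0.01) to the strongest (m = 12, ICC 0.10):

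- SD 10: stays at or above 0.999
- SD 15: 0.986 down to 0.923
- SD 20: 0.878 down to 0.719

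**Psychologist level.** Three psychologists with about 27.5 participants each, assuming an even split: ICC 0.02 gives DE = 1 + 26.5 × 0.02 = 1.53, r = 1.125 and type I error about 8.1%. Large clusters make even a small leader effect count, but three leaders cannot support a reliable variance estimate.

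**The case against.** The strongest reply is that this is silence in a condensed article. The full protocol and analysis plan are not shown, and the handling of a nested arm is often left to them. A reader might infer that the trial treats Face-to-Face participants as independent and that its standard errors are therefore wrong. The document states neither. A sandwich variance can be computed over individuals or over clusters, and naming the estimator does not settle which. This part of the objection stands and limits how firmly the point can be put.

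It does not remove the point. The section fixes the model, the estimator, the sole reason for the robust standard errors and a single per-arm sample size. Carried out as written, these leave therapy group out.

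Second, the size rests on an assumed ICC. At 0.01 the effect is negligible. One range is applied to outcomes as different as weight, sleep and depression, which need not cluster equally. Attrition would also shrink the groups and the design effect. All of this is fair, and it is why a range is shown rather than one figure.

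Third, a reader might conclude that the trial is underpowered. The only stated target is 10 BDI-II points, and its power barely moves at SD 10. The loss becomes clear only with a large SD or a smaller effect, so the documents do not support that conclusion.

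**Conclusion.** The described analysis and sample size do not account for clustering by therapy group in the Face-to-Face arm, and MLR as invoked, for non-normality, does not correct for it. If the within-group ICC is positive, the standard errors of all three Face-to-Face contrasts are too small. For an assumed ICC of 0.01 to 0.10 and groups of 6 to 12, the correct standard error is about 1% to 25% larger, and the type I error is about 5.3% to 11.5% instead of 5%.

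The ICC, the sidedness of the test and the equal variances are assumptions. Whether the error is material cannot be known until the ICC is estimated. The point should be fixed. The documents do not support rating it a must-fix: one arm is affected, the size is uncertain, and the stated power is little changed.

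**What to change.** For every contrast involving Face-to-Face, specify a partially nested model: a random therapy-group effect in that arm only, with participants in the other arms treated as clusters of one. This can be set up as a two-level model in Mplus, which the plan already names, or in mixed-model software. Apply a small-sample degrees-of-freedom correction, because there are only about 7 to 14 groups. Report the ICC for each main outcome. Examine psychologist only descriptively or as a sensitivity analysis, because three are too few for a random effect.

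Cost: the therapy-group identifier is needed for each Face-to-Face participant; the article does not mention it, so its availability should be confirmed. The model is somewhat more complex, and Face-to-Face intervals become somewhat wider. Randomization, treatment and data collection do not change. If the ICC is near zero, little precision is lost.
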